## Abstract

**Background:**

Cervical cancer occurred nearly in 570 000 women and 311 000 women died from the disease worldwide in 2018. Of the new cases diagnosed globally in 2012, approximately 85% of the burden took place in low- and middle-income countries. Human Papilloma virus is the necessary cause for the development of cervical cancer and the majority of these infections resolves naturally but progress to precancerous lesions whenever there is persistence and delay in treatment. Majority of the cervical cancer cases, over 80% in sub-Saharan Africa including Ethiopia, have been detected at a late stage mainly due to poor early preventive measures. Therefore, utilization of early preventive measures could increase timely detection and treatment of precancerous changes and significantly reduce morbidity & mortality due to advanced disease.

**Methods:**

In this interventional study we will randomly assign 16 clusters (kebeles) in to the intervention and the control arm using block randomization. The study will employ a cluster randomized controlled trial. Women are eligible to participate in this study when they satisfy certain eligibility criteria; being in the age range of 30–49 years, no history of hysterectomy, did not receive cervical cancer or pre-cancer treatment and non-pregnant. Home based couple education and counseling will be provided to the eligible participants within the intervention group, while the control group receives standard of care. Base line and end line surveys will be completed by interviewing 288 eligible women to evaluate the effect of couple education and counseling on the knowledge, attitude and cervical cancer screening uptake. Generally the intervention lasts for six months. The results of baseline & end line surveys will be compared between the groups to determine the effectiveness of the intervention. Blinding is not possible due to the clustering of the trial arms.

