Those women who consent to participate in the study will be included and requested to sign an informed consent to ensure voluntary participation. Selected women at each arm will be reached by health extension workers and the data collectors at their home. Once consent is obtained, each participant will be interviewed to complete a baseline survey. The baseline questionnaire includes items on cervical cancer screening knowledge, attitudes, screening experiences, and socio-demographic variables. Similarly end line survey will be conducted at six months.

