### Randomization

The clusters or kebeles are the units of randomization in our study. Initially, eight non-adjacent clusters from each district will be identified from the two districts. Before randomization, we will stratify the clusters by the study districts and create separate list of clusters alphabetically for each district. The stratification will be done to evenly distribute any known and unknown district level confounders across the study arms. Each cluster will be assigned a unique cluster code. Then, the statistician will assign the eight clusters in to two blocks of size 4 according to the order they appeared alphabetically. The statistician will randomly select the randomization sequence of clusters for each block using the sealed lots of the six possible permutations within the block.

The clusters in each block will be randomly assigned to intervention and control arms according to the randomization sequence evident by the selected permutation within in the block for the stratum. We will repeat the same process for blocks of clusters in the other stratum. Consequently, four clusters will be obtained from each district which will form eight clusters to the intervention arm and eight clusters to the control arm maintaining 1:1 random allocation ratio. Both the stratification and randomization techniques will help actual and potential confounding factors distribute evenly across the study arms which will eventually ensure comparability of the arms.

The statistician will be made unaware of the actual study arms to mask the knowledge about which group will receive the intervention and which group will receive the usual care. This will be achieved by representing the study arms and clusters by confidential codes. Health extension workers will carry out identification of eligible participants’ for the study and subsequent intervention administration activities. Assessors will also be made blind to the nature of clusters with respect to intervention administration.

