### Primary outcome

The primary outcome of this study is the completion of cervical cancer screening test within 6 months of the baseline assessment. Participants will be interviewed using the survey questionnaire and tracked via health records review for completing the screening service. The screening proportions will be determined for each study arm at the baseline & end line. The difference in the screening proportions between intervention and control arms will be calculated. Finally, the effectiveness of the intervention will be measured as a difference of the differences in the screening uptake between the study arms.

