### Data collection methods

Data will be collected using structured questionnaire designed for meeting the specific research purpose. The tool has been developed based on the research objectives from relevant literature sources. The data collection instrument will be pretested to check for its clarity, logical sequence, cultural appropriateness etc. and appropriate modification will be made accordingly. Participants will be interviewed to complete baseline survey after randomization of the clusters and end line survey at the end of the intervention period in six months. Participants will be measured for socio-demographic characteristics, knowledge, attitudes, and cervical cancer screening uptake.

Data will be collected through face to face interview technique using paper printed data collection tools contacting each woman at her residential home. Data collectors will go to each selected woman’s home physically by carrying all the data collection tools and communicate verbally with the local language to get the required information. Two different teams will be assigned for the intervention administration and data collection for the purpose of masking the intervention from data collectors. Both the baseline and end line data will be collected by the same individuals to ease the data gathering process.

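### The abstract rules out blinding while the methods claim masked assessors, and the recruitment procedure weakens that masking for the interview-based measurements

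*Protocol article*

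**What the plan says.** **Blinding.** The abstract's Methods paragraph says "Blinding is not possible due to the clustering of the trial arms". The Randomization section says "Assessors will also be made blind to the nature of clusters with respect to intervention administration", and it also keeps the statistician unaware of the arms by means of codes. Data collection methods says "Two different teams will be assigned for the intervention administration and data collection for the purpose of masking the intervention from data collectors".

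**Who visits.** Recruitment of participants says "Selected women at each arm will be reached by health extension workers and the data collectors at their home". On the follow-up survey the same section adds only "Similarly end line survey will be conducted at six months". The Randomization section gives the health extension workers a double role: "Health extension workers will carry out identification of eligible participants’ for the study and subsequent intervention administration activities". Implementation of the intervention says that the workers of the intervention kebeles are trained to deliver it.

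**When, and by whom.** Data collection methods places the baseline interview after randomization of the clusters. That section and Reliability of measures both say that the same collectors carry out both surveys.

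**Outcomes.** For the primary outcome, "Participants will be interviewed using the survey questionnaire and tracked via health records review for completing the screening service". Implementation of screening service adds that every screened woman is entered on a form made for the study. Knowledge and attitude are described only as survey measures.

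**The concern.** The abstract denies a property that two methods sections claim. The reason it gives, clustering, does not prevent masking of outcome assessors. A reader cannot tell from the article which account holds.

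The masking that is claimed rests on keeping the intervention team apart from the data collection team. Recruitment of participants has both groups reaching the same women at home after allocation is fixed, and the health extension worker of an intervention kebele is likely to know the arm. By end line the intervention women have received a brochure and an invitation letter, and the collector is someone who visited before.

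At stake is the direction of any error. Intervention women are encouraged at three visits to be screened, so over-reporting of screening, or generous scoring of knowledge and attitude, would plausibly be larger in that arm. Such error would favour the intervention.

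**Working it through.** **Step 1: the blinding statements compared.**

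| Place | Who is masked |
|---|---|
| Abstract, Methods | Nobody (no qualification) |
| Randomization | Assessors and statistician |
| Data collection methods | Data collectors, through separate teams |

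The first row conflicts with the other two as written. They agree only if the abstract means participants and intervention workers alone, which it does not say.

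**Step 2: the procedure against the claim.** Health extension workers identify participants and deliver the intervention. They and the collectors both reach the women at home, in each arm, after randomization. The same collectors return at six months. The team separation is therefore not clearly kept at baseline. The text does not settle who attends at end line.

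**Step 3: which outcomes are exposed.** Knowledge and attitude come from interview only, so they are fully exposed. The primary outcome comes from interview plus records, so it is partly exposed. How far depends on which source prevails when the two disagree, and the article does not state this.

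**Step 4: the plan's own figure.** A one-sided 5% test with 80% power, 15.5% against 35.5% and a continuity correction needs 68 women per arm. Then 68 × 2 arms × design effect 2 = 272. Allowing for 5% non-response gives 272 × 1.05 = 285.6, or 272 / 0.95 = 286.3. The stated 288 equals 16 × 18, so the sample size reproduces closely. This point does not alter it.

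**Step 5: an illustration of size.** The documents give no misreporting rate, so the bias *b* is assumed. The calculation lets interview answers alone decide the outcome.

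- Documents: 15.5% screened, here taken as the true value in both arms (no effect); 8 kebeles per arm; 18 women each; 5% loss; design effect 2; one-sided 5%.
- Women per kebele after loss: 18 × 0.95 = 17.1. Per arm: 8 × 17.1 = 136.8.
- ICC implied by the planned design effect: 1 + (18 − 1) × ICC = 2, so ICC = 1/17. Design effect at 17.1 women: 1 + 16.1/17 = 1.947.
- SE = √{[0.155 × 0.845 + q(1 − q)] × 1.947 / 136.8}, with q = 0.155 + b.
- Rejection probability: noncentral t with 16 − 2 = 14 df, critical value 1.761, noncentrality b/SE.

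| Assumed over-reporting, intervention arm only | SE | b/SE | Rejection rate |
|---|---|---|---|
| 0 | 0.0611 | 0 | 5.0% |
| 2 points | 0.0626 | 0.319 | 9.0% |
| 5 points | 0.0647 | 0.773 | 18.2% |
| 10 points | 0.0676 | 1.480 | 40.6% |

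**Step 6: a second parametrisation.** Suppose instead that a fraction of the unscreened intervention women are recorded as screened. The spurious difference is then 0.845 × fraction. Fractions of 2%, 5%, 10% and 15% give 1.7, 4.2, 8.5 and 12.7 points. A normal approximation with 144 per arm and design effect 2 (72 effective) rejects in about 9%, 16%, 36% and 58% of trials, which is a similar pattern.

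**The case against.** The case for leaving the plan alone has several good parts.

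- **Recruitment of participants describes consent and baseline**, before any education visit. It names health extension workers in each arm, so a worker's presence does not by itself reveal allocation. This stands.
- **A reader might infer that the worker who coached a woman sits in on her end-line interview.** No section says so. The only link is the word introducing the six-month survey, which may concern timing alone. Data collection methods describes collectors going to each home with their tools and mentions no worker. It is therefore too strong to say that the procedure undoes the masking. What remains is that the text leaves the matter open.
- **A reader might call the primary outcome interview-based.** Records review and the study screening form are both planned, so it is only partly that. The abstract does lean towards interview when it says that the survey results will be compared to judge effectiveness. A rule for discordant sources may sit in a fuller document. Its absence here is no fault in itself, and only means that the protection from records cannot be counted on from this text.
- **The abstract may mean participants and providers only.** That would be compatible with masked assessors, but the sentence needs to say it.
- **Controls are not free of pressure.** Under Standard of care, health extension workers promote screening services to all households. The pressure is unequal, not absent on one side.
- **A records-only outcome has its own bias.** Intervention women are invited to a nearby facility and controls are not. If controls are more often screened elsewhere, a narrow search would undercount them and also favour the intervention. An extractor holding only codes could not match women to a register unless the register carries those codes. Both points stand and shape the fix.

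**Conclusion.** The contradiction between the abstract and the two methods sections is plain and should be corrected. The recruitment procedure weakens the claimed masking of data collectors and provides a route to unmasking. It does not show that masking fails.

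The consequence is a risk of detection bias favouring the intervention. It is greatest for knowledge and attitude, and smaller for the primary outcome because records are also reviewed.

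The size cannot be derived from the documents. The 9%, 18% and 41% rest on assumed over-reporting of 2, 5 and 10 points in the intervention arm only, no true effect, an ICC of 1/17, and interview answers alone deciding the outcome. A reader might take them as the trial's false-positive rate. The planned records review means that they are not. They show only how sensitive the one-sided test would be if records corrected nothing.

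**What to change.** 1. **Reconcile the visit procedure with the masking claim.** State in Recruitment of participants and Data collection methods that health extension workers neither attend nor introduce the interviews, at least at end line.
2. **Fix the deciding source for the primary outcome.** Count a screening as an event when it is confirmed in the study screening form or in facility records. Search these in the same way for both arms, across all screening facilities in the two districts. Give the searcher a linkage list without arm labels. Keep self-report as a sensitivity analysis.
3. **Correct the abstract.** Say that participants and intervention workers are unmasked, and that assessors and the statistician are intended to be masked.

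The cost is some protocol wording, a field instruction, and preparation of the linkage list; the records review is already planned. The downside is that a screening at a facility outside the search could be missed, possibly more often in controls. Cases where self-report and records disagree should therefore be reported by arm. The fix does not remove the risk for knowledge and attitude, which have no record to check against. For those outcomes the first change is the main protection.

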**Discussion:**

Findings of the study will inform the regional or national scale up of the intervention modality to achieve the screening targets set by the Ethiopian government and world health organization.

**Trial registration:**

PACTR, PACTR202108529472385. Registered on 05 August 2021, https://pactr.samrc.ac.za/TrialDisplay.aspx?TrialID=16037

## Introduction

Human Papilloma Virus (HPV) is the necessary cause for the development of cervical cancer. Nearly all sexually active women are infected with HPV during their lifetime but majority of the infections resolve naturally within 24 months [1]. However, approximately 12% of these acute infections become persistent and can progress to precancerous lesions or invasive cervical cancer over decades, when not detected and treated early [2]. https://www.ncbi.nlm.nih.gov/pmc/articles/PMC5519520/pdf/fpubh-05-00178.pdf The precancerous lesions progress to advanced cancer stages usually within 10 to 20 years. This extended course in the progression of HPV infection to advanced cancerous stage provides an opportunity for the implementation of effective screening programs to prevent the development of cervical cancer through early detection and treatment modalities [1].

In 2012, the global cancer statistics showed that there were an estimated 527,600 new cervical cancer cases and 265,700 deaths worldwide [3]. Also, in 2018, cervical cancer occurred nearly in 570 000 women and 311 000 women died from the disease globally [4]. Cervical cancer in low- and middle-income countries (LMICs) accounted for approximately 85% of new cases and 87% of deaths that occurred globally in 2012 [5]. But in resource-rich countries the incidence and mortality due to cervical cancer were two to four times lower than what had been seen in resource scarce countries. The highest disease burden was demonstrated in southern and eastern Africa [4]. These statistics describe that there have been disproportionately heavy burden of cervical cancer among women in less developed regions of the world [1].

Larger proportions of cervical cancer cases and deaths occurred in Sub-Saharan African countries in 2018. Of the highest regional incidence and mortality rates observed in Africa, Eastern Africa shared the highest mortality rate due to cervical cancer in the year [6]. Also studies reported that the highest prevalence of cervical infection with HPV is recorded in Sub-Saharan Africa (SSA) countries [7]. Based on the projections made by World Health Organization (WHO), cervical cancer will be responsible for 443,000 deaths in 2030 globally [8] of which 98% will occur in low income countries, with SSA facing the highest number of deaths [5].

In Ethiopia, in a trend analysis of the cancer registry data, 5293 cervical cancer cases were diagnosed between 1997 and 2012 and accounted for 31.8% of all new cancer cases [9]. Also the trend analysis of cancer from 1998 to 2010 in Ethiopia showed that, malignancy involving cervix is among the leading malignancies in the country [10]. The estimated number of new cases of cervical cancer was 6047 with age specific incidence rate of 22% that accounts for about 20% of all identified female cancer cases in 2015 [11]. According to world’s summary report, about 6,300 new cervical cancer cases and 4,884 deaths due to cervical cancer occur each year in Ethiopia that makes cervical cancer the second-most common, and the second-most deadly cancer in the country among the target group [12].

Cervical cancer incidence and mortality have been considerably reduced in high resource countries during the last few decades. This is mainly due to the implementation of screening packages for the detection of precancerous cervical lesions and HPV infection. The availability of improved treatment options also played their role in this regard [13]. However, in low- and middle income countries where access to screening and treatment services is limited, cervical cancer remains a significant public health problem [6].

As a cervical cancer preventive measure, the Ethiopian Federal Ministry of Health (FMOH) in collaboration with the Pathfinder piloted Visual Inspection with Acetic acid (VIA) screening services combined with access to cryotherapy in 2009 for people living with Human Immunodeficiency Virus (HIV). These services have been later on scaled up into public healthcare facilities and standardized with the subsequent development of comprehensive cervical cancer prevention and control guideline in 2015 [14]. Nearly 1% of age-eligible women ever received screening in Ethiopia before the implementation of this guideline [15]. But more recent studies reported an uptake of 9.9% –15.5% in selected populations in Southern and Southwest Ethiopia [16–18]. Though the progress shows a favorable trend, it is far away from 80% target coverage nationally set for the 30–49 years target population by 2020 [19] which calls urgent public health interventions.

Evidence suggests that the availability and utilization of screening programs combined with effective treatment options lead to a significant reduction in the morbidity and mortality associated with advanced cervical cancer. In Ethiopia, despite the availability of screening services, only few of the eligible women underwent screening for cervical pre-cancer. Moreover studies have not been conducted to determine the effectiveness of locally adapted interventions which could increase cervical pre-cancer screening uptake among eligible women. Our research, therefore, aims to test the effectiveness of leaflet assisted home based couple education and counseling on knowledge, attitude and uptake of cervical cancer screening among eligible women.

## Methods

### Objectives

The objective of this study is to determine the effectiveness of leaflet assisted home based couple education and counseling in increasing the knowledge, attitude and uptake of cervical pre-cancer screening services among eligible women. Two groups of women are compared where the intervention group receives home based couple education and counseling while the control group receives the usual standard of care available in routine service delivery schemes.

### Trial design

This study is a two arm parallel cluster randomized trial that will be conducted in the Southern people regional state of Ethiopia.

### Study setting

The geographic location for our study is Kembata Tembaro and Hadiya zones which are located in the Southern Nations Nationalities and Peoples’ Regional State. The total number of age eligible women (30–49 years) for cervical cancer screening in the study zones constitutes 19.2% of women of reproductive age group residing in the zones. Kembata Tembaro zone comprises 8 districts and 3 city administrations with the total number of 150 clusters or kebeles, the smallest administrative units, of which 9 are located in the city administrations. The zone has one general hospital, four primary hospitals, 33 health centers and 138 health posts. Hadiya zone is administratively organized in to 13 districts and 4 city administrations having a total number of 329 clusters. The zone has one comprehensive specialized hospital, three primary hospitals, 61 health centers and 317 health posts.

The health care of women of child bearing age in general and maternal & child health care services in particular are of the main strategic pillars of the health service delivery efforts in the zones. Cervical cancer prevention and control activities are being integrated in to the routine health care delivery as an important health service package for the women’s health. Currently, cervical cancer screening services are being implemented at selected hospitals and health centers of the zones where our research activities will base these facilities.

